### Follow-up visits

**Day seven:** follow-up visit seven days after the therapeutic aspiration (can be done 5–10 days). This is part of standard clinical care for patients to receive results of pleural fluid testing and decide a management plan. Patients standardly have a CXR at this visit and this will be used to reassess size of effusion. At the point, the 7DVQ will be collected and a CRF completed, particularly to assess whether participants have required further pleural fluid drainage or attended the hospital with breathlessness during the seven-day period. During this period the participant is permitted to have any clinically required intervention.
**Second pleural procedure:** this will be performed if clinically indicated for diagnostic or symptomatic reasons. Indications for symptomatic drainage are as follows: symptomatic benefit from initial pleural fluid drainage; significant breathlessness; and significant pleural effusion (defined as at least 25% of the hemithorax on CXR or estimated volume of pleural fluid of at least 500 ml using US). Participants will undergo a further pleural drainage (
*via* thoracoscopy, chest drain or indwelling pleural catheter insertion according to clinical requirement in their individual care pathway). Patients will undergo CXR and US at this visit prior to intervention.
**Day 30:** follow-up by telephone/review of hospital records to determine further pleural procedures, emergency hospital attendances, other treatment for effusion
*e.g.*, chemotherapy, surgery, diuretics.
**Three months:** follow-up by telephone/review of hospital records to determine further pleural procedures, emergency hospital attendances, other treatment for effusion
*e.g.*, chemotherapy, surgery, diuretics. We will also collect health related QoL data using the EQ-5D 5L questionnaire by telephone.

Research staff will informally assess capacity at each follow-up visit. If the investigator believes that the participant has lost capacity to consent, no further data will be collected, and they will be withdrawn. The study data and samples will be used/retained if the participant had consented for this during the initial consent process.

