There has been little research to date studying predictors of pleural fluid reaccumulation. One previous retrospective cohort study found that the size of effusion on CXR prior to therapeutic aspiration, the volume of pleural fluid drained during therapeutic aspiration, the pleural fluid lactate dehydrogenase (LDH) levels and positive pleural fluid cytology predicted a further pleural drainage procedure being carried out in a single centre with a highly protocol-led pathway
^
10
^. However, these variables were not predictive in other centres. This paper demonstrated wide variation in time to a further drainage procedure, with 30% of patients requiring a further procedure within 15 days whereas 52% had not had another procedure at 90 days. Boshuizen
*et al.*, also found that the volume of pleural fluid drained was predictive of need for a further pleural intervention
^
11
^.

 Despite the lack of evidence for predictors of pleural fluid recurrence, our survey demonstrated that 71% of clinicians try to predict how quickly pleural fluid will recur. However, there was no consistent method for doing this. Clinicians based this judgement on variables such as the speed of onset of symptoms, initial size of the effusion, tumour type and previous recurrence rate (based on review of previous radiology/time between previous drainages).

**
*Data from feasibility study*
**

We successfully recruited 20 patients to a feasibility study at the Norfolk and Norwich Pleural Unit from January to July 2019. We screened 40 patients attending the Pleural Clinic for a therapeutic aspiration of their effusion for eligibility and identified 23 eligible patients. Of these, 20 consented to enrolment. All enrolled patients attended the one-week primary outcome follow-up. The feasibility study included qualitative interviewing of the patients and patients were asked about their experience of the study as part of this interviewing. Our results demonstrated that this study is acceptable to patients and recruitment to target is feasible.

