### Objectives and outcome measures

The primary objective of this study is
**t**o identify candidate biomarkers associated with the rate of pleural fluid accumulation in patients with MPE and to use these biomarkers to develop and validate a clinical score to predict rate of reaccumulation. These biomarkers will be measured at day 0. This will be compared with the rate of pleural fluid accumulation based on increased size of pleural effusion from CXR immediately post-aspiration to day 7
^
12
^.

*Complete list of candidate biomarkers to be assessed for the primary objective*

The candidate biomarkers include:

Patient biomarkers: i) duration of symptoms; type of malignancy; ii) known malignancy or first presentation; iii) severity of pre-procedure breathlessness (measured on visual analogue scale); iv) previous chemotherapy and/or radiotherapy and/or immunotherapy; v) current chemotherapy and/or radiotherapy and/or immunotherapy; vi) current use of diuretics; emergency (
*via* Accident and Emergency (A&E) or acute medical unit) or urgent presentation (
*via* General Practice (GP) or oncology); vii) performance status (assessed using Eastern Co-operative Group scale); and viii) co-morbidities (chronic renal failure, liver disease, cardiac failure).Effusion biomarkers: i) size of effusion on pre-procedure CXR (measured as percentage opacification of hemithorax - this is a validated measure of effusion size); ii) size of effusion on pre-procedure US (measured from hemidiaphragm to top of effusion); iii) side of effusion; iv) volume of fluid drained during therapeutic aspiration (ml); v) degree of pleural fluid septations (categorised as none, mild, moderate or severe) on US; vi) significant non-expandable lung on post-procedure CXR; and vii) pleural pressures measured by manometry (substudy in 20 patients only in Norwich).Pleural fluid biomarkers: i) total protein; ii) pH; iii) glucose; iv) lactose dehydrogenase (LDH); and v) cytology (categorised as positive
*i.e.*, malignant cells present or negative).Serum biomarkers: i) haemoglobin; ii) white cell count, including neutrophil and leukocyte subsets; iii) C reactive protein; iv) total protein; v) estimated glomerular filtration rate (eGFR); vi) LDH; and vii) N-terminal pro-brain natriuretic peptide (NT-proBNP).

**
*Why were these biomarkers chosen?*
**

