**Inclusion in analysis**
*

All participants with available data will be included in the day seven analysis. For the one month and three-month outcomes, all participants including those lost to follow-up or who die within the time period will be included in analysis.

*

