**Assessment of effusion size on CXR**
*

Percentage opacification of the hemithorax by effusion will be measured on the post-procedure and follow-up CXR. This is a validated measure of effusion size performed using freely available software (
PaintShop Pro 2022 (RRID:SCR_000338), Corel Corporation and
ImageJ version 1.53r (RRID:SCR_003070),
National Institutes of Health (RRID:SCR_011417)). Anonymised digital CXR images will be uploaded onto the study database. PaintShop Pro is used to outline the hemithorax and effusion. These shapes are then converted into a pixel count by ImageJ. Percentage opacification is calculated by dividing the effusion pixel count by the hemithorax pixel count. This analysis takes approximately five minutes per image.

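### The primary outcome is read from the day-7 X-ray even after an early repeat drainage, which understates reaccumulation in some of the fastest patients and biases associations towards zero

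*Protocol article*

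**What the plan says.** All places are in the Protocol article.

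- **Outcome.** Objectives and outcome measures sets the target as "rate of pleural fluid accumulation based on increased size of pleural effusion from CXR immediately post-aspiration to day 7".
- **Film used.** Follow-up visits, day seven: "Patients standardly have a CXR at this visit and this will be used to reassess size of effusion". Assessment of effusion size on CXR: "Percentage opacification of the hemithorax by effusion will be measured on the post-procedure and follow-up CXR".
- **Timing.** The visit is a "follow-up visit seven days after the therapeutic aspiration (can be done 5–10 days" window. No scaling to the actual interval is described.
- **What may happen in between.** "During this period the participant is permitted to have any clinically required intervention". The day-7 case report form records whether further drainage was needed, but no analysis of that item is stated.
- **Second procedure.** It may be symptomatic or diagnostic. The symptomatic indication combines benefit from the first drainage, significant breathlessness, and an effusion of at least 25% of the hemithorax on CXR or 500 ml on ultrasound. "Patients will undergo CXR and US at this visit prior to intervention".
- **Analysis set.** Inclusion in analysis: "All participants with available data will be included in the day seven analysis".
- **Missing data.** The rule there covers loss to follow-up or death before three months. It concerns later procedures, not the day-7 film.

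**The concern.** The three rules do not fit together: a fixed day-7 film, unrestricted drainage before it, and inclusion of everyone who has the film. If fluid returns fast enough to be drained on, say, day 3, the day-7 film shows what is left after that drainage. The computed change is then small although the true reaccumulation was large.

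The score is meant above all to identify rapid reaccumulators, so the error falls on the patients who matter most. It pulls estimated associations towards zero and lowers R². The internal bootstrap validation and the Phase 2 validation cohort measure the outcome in the same way, so good apparent agreement there would not reveal it. Excluding these patients would not solve it either, because that removes part of the upper tail of the outcome.

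**Working it through.** **1. The plan's own figures.** Inputs from Sample size and analysis plan: n = 150, 8 parameters, R² = 0.5, mean 14, SD 13.

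- Apparent R² = (0.5 × 141 + 8)/149 = 0.527.
- Shrinkage = 1 + (8 − 2)/(150 × ln(1 − 0.527)) = 0.947 (stated 0.95).
- Optimism in R² = 0.527 − 0.5 = 0.027 (stated within 0.05).
- Residual SD margin = √(141/χ²(0.025; 141)) = 1.132, or 13%.
- Half-width of the mean = t × √(13² × 0.5/150) = 1.48 (stated 1.5).
- 150/8 = 18.75.

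All reproduce, so the mean, SD and R² are a fair base for the next steps.

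**2. Is early drainage plausible?** With a normal outcome, the probability of a gain of at least 25 points by day 7 is 1 − Φ((25 − 14)/13) = 1 − Φ(0.846) = 0.199. This is not a drainage rate: the 25% criterion is absolute size, ultrasound volume is an alternative, and breathlessness and prior benefit are also required. It shows only that effusions of that size are expected within the week. The article gives no 7-day re-drainage share, so the share f is an assumption below.

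**3. Effect of recording a post-drainage film.** Let the true 7-day change Y be normal (14, 13²), with a predictor X explaining half its variance. The fraction f with the largest Y is drained and then recorded at the value c. With t = Φ⁻¹(1 − f) and u = (c − 14)/13, the slope of the recorded outcome on X is

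Φ(t) − tφ(t) + uφ(t).

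Example, f = 5%, c = 0: t = 1.645, φ(t) = 0.103, u = −1.077, so 0.950 − 0.170 − 0.111 = 0.67. Simulation of 1,000,000 patients agrees and supplies R². In the noisy version, who is drained depends on a score correlated 0.7 with Y.

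| f | Patients of 150 | Slope, strict | R², strict | Slope, noisy | R², noisy |
|---|---|---|---|---|---|
| 0 | 0 | 1.00 | 0.50 | 1.00 | 0.50 |
| 2% | 3 | 0.83 | 0.38 | 0.89 | 0.42 |
| 5% | 7.5 | 0.67 | 0.28 | 0.79 | 0.34 |
| 10% | 15 | 0.49 | 0.17 | 0.66 | 0.25 |

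All rows take c = 0. With c = +5 and strict selection the slopes are 0.85, 0.71 and 0.55; with c = −10 they are 0.79, 0.59 and 0.35.

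**4. Consequence for the sample size.** Putting the reduced R² into the shrinkage formula:

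- R² = 0.28: apparent R² = (0.28 × 141 + 8)/149 = 0.319, shrinkage about 0.90.
- R² = 0.17: apparent R² = (0.17 × 141 + 8)/149 = 0.215, shrinkage about 0.83, below the 0.9 that the plan cites as recommended.

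**5. Direction.** For c = 0 or +5 the slope stays positive at every f up to 70%. For c = −10 with strict selection it turns negative only above f of about 22%. In 4,000 samples of 150 with c = 0, no slope was negative at f = 5%, 10% or 15%; 0.03% were at 20% and 1% at 25%.

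**6. Alternatives.** Strict selection, slopes at f = 5%, 10% and 20%:

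- Early-drained patients excluded: 0.89, 0.83, 0.74.
- Pre-procedure film used, not scaled for time (drainage on days 3 to 6): 0.88, 0.82, 0.74.
- Pre-procedure film divided by days elapsed: 1.00 throughout. This follows from the linear accumulation built into the calculation.

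**The case against.** **The article never says outright that patients drained early keep the day-7 value.** The second procedure is listed among the follow-up visits, with its own CXR, so the follow-up film could be read to include the pre-procedure one. That reading conflicts with an outcome that runs to day 7 and with the statement that the day-7 film is used to reassess size. The consequence is drawn from the definition, but it is the natural reading.

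**This is a condensed article and details may sit elsewhere.** True, and a rule in the full protocol would settle the matter. But the point does not rest on silence: the article fixes the film, permits the drainage and defines the analysis set.

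**The size is unknown.** This stands. A reader might spread the cited "30% of patients requiring a further procedure within 15 days whereas 52% had not had another procedure at 90 days" at a constant hazard and get 1 − 0.7^(7/15) = 15% by day 7. The same sentence contradicts that: a constant hazard leaves 0.7^(90/15) = 0.7⁶ = 12% without a procedure at 90 days, against the 52% reported. Management is also decided at the day-7 visit, so procedures may cluster after the outcome film, and patients drained at that visit after their CXR are unaffected.

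**Early drainage is not a clean marker of speed.** This stands too. Residual fluid, symptoms and diagnostic reasons all play a part, which is why the noisy version is shown. It is milder, but the attenuation remains.

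**Conclusion.** The concern holds as a bias towards zero in the primary outcome analysis. Followed as written, the outcome rule understates reaccumulation in patients drained again for symptoms before the follow-up film, and the planned validation cannot detect it. For assumed shares of 2% to 10%, the slope lies between about 0.89 and 0.49 and R² between about 0.42 and 0.17, depending on how strictly drainage selects the fastest patients. These figures rest on the plan's mean, SD and R², on normality, and on a recorded change of zero after drainage. The true share could be smaller or larger.

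A reader might infer that the model would learn the wrong direction. The documents do not support that: reversal needs more than about 22% drained, strictly the fastest, and each recorded 10 points below their own post-aspiration film. Nor do they support treating everyone drained early as a fast reaccumulator, since diagnostic procedures are allowed.

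**What to change.** Define the primary outcome as opacification on the last CXR before any second pleural drainage, minus opacification on the post-aspiration CXR, divided by the days between the two films. For anyone drained before the follow-up visit, use the pre-procedure CXR that the protocol already obtains. For everyone else, use the follow-up CXR with its actual interval. This also handles the 5–10 day window: at the assumed mean of 14 points in 7 days, or 2 per day, the same rate gives 10 points at day 5 and 20 at day 10.

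Add a sensitivity analysis for patients drained early that separates symptomatic from diagnostic procedures. Placing all of them at the top of the outcome scale would misclassify the diagnostic ones. Report how many were drained before the film, and settle the rule before the outcome is analysed.

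The cost is wording in the outcome definition and reading one existing image per affected patient, at about five minutes each by the article's own estimate. The downsides are noisier rates over short intervals and an assumption of roughly linear accumulation, which should be stated. No change to clinical management is implied.

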### Pleural fluid and blood Sample handling (optional long-term storage)

Pleural fluid and blood samples will be processed after taking and centrifuged according to the study specific procedures. They will then be stored locally in a freezer at -80°C. Samples will be stored and may be used for exploratory analysis such as proteomics analysis and measurement of individual biomarkers.

### Discontinuation/withdrawal of participants from study

Participants may withdraw from the study at any time. The research team may also withdraw a participant if necessary, for example for the following reasons: 

Identification of exclusion criteria
*e.g.*, pleural infectionInability to perform therapeutic aspirationPregnancySignificant protocol deviationWithdrawal of consentLoss to follow-up

If provided, the reason for withdrawal will be recorded in the CRF. Data and samples collected prior to withdrawal will be included in analysis unless the participant requests that they are not used. If the participant loses capacity and they had not consented for their study data/samples to be retained following loss of capacity to consent, their data/samples will not be used.

### Definition of end of study

The end of study is the date when all sample analysis is complete.

### Distress protocol

We recognise that patients attending the Pleural Clinic may find the experience distressing, due to anxiety over the possible cause of their pleural effusion or having to undergo an invasive procedure. They may become distressed during trial procedures, and it is imperative that the researcher responds to this distress in a sensitive and reassuring manner.

The distress protocol is as follows:

1.A participant indicates that they are experiencing a high level of stress or emotional distress OR exhibits behaviours suggesting the trial procedures are too stressful
*e.g.*, uncontrolled crying, shaking.2.Stop the trial procedures. One of the researchers or clinical team will offer immediate support by reassuring the patient and exploring the reason for their distress.3.If the participant feels able to carry on, then trial procedures can be continued. It is important that the participant is aware they can withdraw from the trial at any point.4.If the participant feels unable to carry on, then stop trial procedures and continue to reassure them. Remind them of the support that is available to them during this process
*e.g.*, from the specialist nursing team.5.If the participant requests to withdraw from the study, then their wishes will be respected.

### Statistics and data analysis

**
*Description of statistical methods*
**

Reporting will include the number of patients screened for inclusion, the number of participants completing the study and exploratory analysis of any correlations between baseline factors and change in size of effusion on CXR.

*
**Sample size and analysis plan**
*

Based on our feasibility data, we estimate we need to recruit 200 patients to have complete data available on 150 patients. The main reason for this is that approximately 20% of patients will turn out not to have MPE and therefore will not be eligible for inclusion in the final analysis. The primary outcome measure is at one week and is part of standard clinical care and therefore we anticipate that loss to follow-up, withdrawal rates and missing data will be minimal based on our feasibility data and previous trial experience. A further validation cohort of 40 patients will be recruited subsequently. Follow-up will be either by review of available medical records, telephone or clinical appointment (if patient is coming up to hospital anyway) at 30 days and three months.

A sample size of 150 participants would allow us to have a shrinkage factor of 0.95, which is above the recommended 0.9, assuming an R
^2^ value of 0.5 and 8 parameters in the model. It would also allow the estimated R
^2^ value to be within recommended limits of 0.05 of the true R
^2^ value. It would allow the estimation of residual standard deviation to be within 13%. Although this is above the recommended 10%, we believe that it is still clinically meaningful. It also allows the estimation of the mean outcome to within +/- 1.5%, which is sufficiently precise to be clinically useful, assuming an overall mean of 14 and an SD of 13. This represents 18.75 individuals per variable, which is within the traditional 10–20 individuals per variable rule-of-thumb. The analysis will be based on traditional regression methods and follow the Transparent reporting of a multivariable prediction model for individual prognosis or diagnosis (TRIPOD) statement
^
16
^. An outline of the analysis is as follows:

1.Initial screening of potential predictor variables to ensure that there is sufficient variation in them and that they are not missing at an unreasonably high level. For example, if a categorical variable does not have >5% of participants in any category; or if a continuous variable does not cover a broad enough range. After the initial screening, if appropriate data reduction techniques such as principal component analysis will be undertaken to reduce the number of variables to a reasonable amount.2.Model selection will then be undertaken using variable selection such as backwards elimination. Continuous covariates will be checked for non-linear relationships using splines.3.Once an appropriate model has been selected, the optimism and internal validation will be estimated using a non-parametric bootstrap approach. If overfitting if found to be an issue, then penalised regression (Lasso or Ridge regression) will be used to reduce the amount of overfitting.4.Once the final prediction model has been estimated, its properties such as discrimination by the estimation of the R
^2^ and calibration by plotting the observed outcome against the predicted outcome will be explored. If there is a large number of participants excluded due to missing predictor variables, then the sensitivity of the final prediction model to missing data will be assessed using multiple imputation.

*

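### The sample-size section states R² will be estimated to within 0.05 of its true value; what meets 0.05 is the expected optimism (0.027), while the 95% sampling precision of R² at n = 150 is about ±0.11

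*Protocol article*

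**What the plan says.** The section on sample size and analysis plan in the protocol article gives four properties of the design in sequence.

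- Shrinkage: "A sample size of 150 participants would allow us to have a shrinkage factor of 0.95", under an assumed R² "value of 0.5 and 8 parameters in the model".
- R²: the same sample is said to allow the estimated R² "value to be within recommended limits of 0.05 of the true R"², the quotation ending just before the superscript.
- Residual standard deviation: "It would allow the estimation of residual standard deviation to be within 13"%. The text admits that this exceeds a recommended 10%.
- Mean outcome: "It also allows the estimation of the mean outcome to within +/- 1.5"%, "assuming an overall mean of 14 and an SD of 13".

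The analysis outline that follows names R² as the measure of the final model's discrimination, to be considered alongside a calibration plot.

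**The concern.** A statement about how far an estimate lies from the true value is a statement about sampling precision. The sentences after it, on the residual standard deviation and the mean, are margins of error, so nothing tells the reader to take the R² sentence in another sense. Taken at its word, it means that a reported R² of 0.50 could be read as 0.45 to 0.55.

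Optimism and sampling error are different things. Optimism is a bias: the average amount by which a model looks better in the data it was fitted to. It can be estimated and removed, and the planned bootstrap does so. Sampling error is the scatter of the estimate from one study to the next, and correcting for optimism does not reduce it. If the first is described as the second, readers will place more confidence in the reported R² than 150 patients can support.

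**Working it through.** **Inputs**, all from the section on sample size and analysis plan: n = 150; p = 8 parameters; R² = 0.5; outcome mean 14 and SD 13. The residual degrees of freedom are n − p − 1 = 141. A 95% confidence level is assumed, because the section states none.

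**Step 1. Reproduce the plan's own figures.**

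- Expected apparent R² = [R²(n − p − 1) + p]/(n − 1) = (0.5 × 141 + 8)/149 = 0.527.
- Shrinkage = 1 + (p − 2)/[n ln(1 − apparent R²)] = 1 + 6/[150 × ln(0.473)] = 0.947. Stated: 0.95.
- Optimism = p(1 − R²)/(n − 1) = 8 × 0.5/149 = 0.027. This is below 0.05.
- Residual SD margin = √(141/χ²) = 1.132, where χ² is the 2.5% point on 141 degrees of freedom. That is 13.2%. Stated: 13%.
- Mean half-width = t(0.975, 141) × √(13² × 0.5/150) = 1.48 outcome units. Stated: 1.5.

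All four figures fit one coherent set of criteria, with the 0.05 acting as a limit on optimism.

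**Step 2. Test the sentence as worded**, as closeness of the estimate to the true R².

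- Large-sample standard error: √{4R²(1 − R²)²(n − p − 1)²/[(n² − 1)(n + 3)]} = √{4 × 0.5 × 0.25 × 141²/(22,499 × 153)} = 0.054. Half-width: 1.96 × 0.0537 = 0.105.
- Simpler form: √{4R²(1 − R²)²/n} = √(0.5/150) = 0.058. Half-width: 0.113.
- Fisher z interval around R² = 0.5: 0.38 to 0.61.

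**Step 3. Simulation.** There were 20,000 studies of 150 patients with eight independent normal predictors of equal effect and a true R² of 0.5. All eight predictors were fitted, with no variable selection.

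| Estimate | Mean | SD | 95% range | Within 0.05 of truth |
|---|---|---|---|---|
| Apparent R² | 0.524 | 0.057 | 0.41 to 0.63 | 57% |
| Adjusted R² | 0.496 | 0.060 | 0.37 to 0.61 | 60% |

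Adjustment moves the mean back to about 0.5 but leaves the spread essentially unchanged. Every method gives a 95% half-width of about 0.11, roughly twice the stated 0.05.

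**The case against.** The strongest reply is that nothing has been miscalculated. The other three figures reproduce from the stated inputs, and the reference to a recommended limit, placed among those criteria, points to the gap between apparent and adjusted R². In that sense the limit is met with room to spare. The section also gives no confidence level for R², and it is open about missing the residual SD limit. Much of this stands: the calculation behind the sentence appears sound. But knowing which criterion was probably meant explains the sentence without making it true. It speaks of the true R², and at about 60% coverage no usual confidence level would rescue it.

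Two stronger readings are tempting and are not supported.

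- *The sample is too small for R².* A reader might infer that a precision target has been missed and that more patients are needed. The document does not set a sampling-error target of 0.05 as a design requirement that can be told apart from the optimism limit, and 150 patients satisfy that limit.
- *The mean also misses a target.* A reader might divide 1.48 by 14, get 10.6%, and set it against 10%. The section ties the 10% limit to the residual SD only. For the mean it cites no limit and simply calls the precision clinically useful. The section on assessing effusion size says: "Percentage opacification of the hemithorax by effusion will be measured on the post-procedure and follow-up CXR". A margin of 1.5% is therefore naturally read in the outcome's own percentage units, where it reproduces. It uses the residual variance and so depends on R² = 0.5, but that assumption is stated earlier in the same paragraph. With the full SD of 13 the half-width would be 2.1, which answers a different question. This is at most an ambiguity of unit.

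The defence is also right that the planned bootstrap, the calibration plot and the commitment to TRIPOD reporting limit the practical harm. How the interval for R² will be reported can be left to the analysis plan.

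**Conclusion.** The point holds as an error of statement. The section attributes to the design a precision for R² that it does not have: about ±0.11 at 95% (0.105 to 0.113 by formula; roughly 0.37 to 0.61), against a stated 0.05. What lies under 0.05 is the expected optimism of 0.027. Neither the sample size nor the underlying criterion is in error, and no planned analysis is affected.

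The conclusion assumes a true R² of 0.5, eight fitted parameters, 150 complete cases and a 95% level. The simulation further assumes normal predictors and no data-driven selection. That the 0.05 was meant as a limit on optimism is an inference from the way the neighbouring figures reproduce; the document does not say so.

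**What to change.** Replace the R² sentence with wording such as: *the expected difference between apparent and adjusted R² is about 0.03, below the 0.05 limit; the 95% half-width for R² at n = 150 is about 0.11.*

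Optionally, for clarity only, give the mean's margin as *±1.5 percentage points (assuming R² = 0.5)*.

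The cost is a change of wording, with no change to enrolment or analysis. The downside is that the published precision for R² becomes less favourable than the one now stated.
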